### Temporal patterns in hospital falls and relative risks of fall

Although important efforts have been made to identify possible risk factors for falls, the time of falls has often been ignored. With regard to the occurrence of accidental falls, it is important to know not only the time of day and the shift work of the healthcare professionals (especially nurses, who are responsible for the data collection) but also the relative risk of intrinsic and external factors (*chronoepidemiology*), as well as circadian rhythms related to the clinical care of patients and healthcare workers [19, 20]. Recent studies of our research group [5, 20, 21] observed that the time of the day, the day of the week and the month of the year have impacts on the fall occurrence. Concretely, a retrospective study [20], carried out in five different non-teaching public Italian hospitals after the development of a programme to prevent falls, identified 24-hour and seasonal patterns for accidental falls in hospitals among a population older than 65 years old and showed crucial information about the relationships between the circumstances of falls (cause, mode and place) and times of falls. On the other hand, the extension of preventive measures according to the obtained temporal patterns (*chronoprevention*) affected the reduction of the number of falls in hospitals, although, due to the retrospective nature of the study and the association with other institutional measures not included in the study, a possible direct effect was not established.

In addition to the research carried out in our group, several studies have been focused on the topic, which is an important indicator of the increasing importance of the research field among the scientific community [22, 23]. Both studies confirmed the finding of a morning peak in hospital falls strictly related to bathing activities. In fact, as consequence of the results published by Magota [23], a letter to the editor was published in order to promote more comprehensive research about accidental falls focused on temporal patterns [24].

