Support and instruction to the patient in preventive health measures (wear suitable footwear and, when necessary, include orthoses; repeated reminders to patients of the need to notify the team for any situation (getting up/lying in bed, going to the bathroom/shower, walking in the hallways, …)).Take extreme measures to prevent falls by healthcare professionals at times related to meals and transfers.Placing a poster encouraging the need to review medication(s) at admission and periodically through patient monitoring.Patient risk management procedures, including post-fall monitoring, alternatives to restrictions and/or restrictive elements, increased number of nursing visits to the patient, promotion of safe mobility and bathing practices based on specific clinical guidelines (Register Nurses’ Association of Ontario, 2011) and use of proper closed footwear.Monitoring and improvement in the distribution of work shifts in healthcare professionals.

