Simple and multi-component Cosinor analyses will be used to explore temporal patterns [34]. This analysis uses the least squares method to approximate the time series of data to obtain one or more harmonics that fit the wavy shape that best explain the variance of the data set. The proportion of the overall variance (PR) represented by each harmonic component and the final multi-component curve function serve as goodness of fit parameters; the higher the PR is, the better representation by the total variance of the harmonic. The F-test statistic applied to the variance, represented by an approximation of the cosine curve versus a linear approximation of the time series data, was used to reject the null hypothesis of zero amplitude (absence of cyclical variation with respect to the period of time explored). The statistical significance of temporal patterns will be verified when the null hypothesis rejected for the F-test statistic is p < 0.5. The descriptive parameters of the statistically significant temporal patterns are the statistical estimated mean rhythm line (MESOR, the estimated rhythmic mean of the time series), amplitude (A, the numerical difference between the peak and valley values), temporal peak (φ, orthophase) and temporal valley (bathyphase); these last two variables are expressed according to the local midnight (00:00 h). The prominence of the temporal patterns, in terms of amplitude, will be expressed according to the MESOR as % AMP (greater prominence of the temporal variation, if the % AMP is greater). The variation will be low if % AMP < 25, moderate if 26–50, and high if > 50. To carry out the simple and multi-component Cosinor analyses, Chronolab software will be used [34].

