The findings that are expected to be found will be transferable to the institution and, in addition, the expected decrease in the incidence of falls will mean a reduction in healthcare costs. The findings endorsed by previous studies carried out in Italian hospitals [20, 39] showed interesting results.

The hourly categorization of fall events according to the evaluated intrinsic and extrinsic risk factors allows for a more precise understanding of their epidemiology and, ultimately, the improvement of the instituted prevention programme. Therefore, the results are likely to generate clinical practice guidelines [6, 24].

The results of this project are intended to promote a more exhaustive investigation of falls, thereby improving initiatives for their prevention. Furthermore, the study interventions emphasize the importance of recording in-hospital falls and their circumstances, especially time. The proposed registration system could be easily implemented and represents a change in health policy. The application of preventive measures according to time (*chronoprevention)* applied in this study will influence the reduction in the number of hospital falls considerably.

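### If falls are collapsed to 24 hourly totals, the Cosinor F-test counts lack of fit as error and may miss peaks of a few hours; a count-based test of the same harmonics would lose much less

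*Protocol article*

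**What the plan says.** The main dependent variable is the number of hospital falls, and the hour and minute of each fall are recorded (Study variables). For time patterns the Data analysis section states: "Simple and multi-component Cosinor analyses will be used to explore temporal patterns". The fit is by least squares: "This analysis uses the least squares method to approximate the time series of data to obtain one or more harmonics", with no maximum number of harmonics. The test of zero amplitude is described as "The F-test statistic applied to the variance, represented by an approximation of the cosine curve versus a linear approximation of the time series data". Peak, valley, amplitude and MESOR are listed as descriptors of statistically significant patterns only.

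Two thresholds appear in the same section. The general rule is p < 0.05 for all tests. For the Cosinor: "The statistical significance of temporal patterns will be verified when the null hypothesis rejected for the F-test statistic is p < 0.5".

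The unit of the series is not stated. The nearest hint is in the Discussion: "The hourly categorization of fall events according to the evaluated intrinsic and extrinsic risk factors". On the expected pattern, the Background cites "a morning peak in hospital falls strictly related to bathing activities", and one of the planned measures concerns prevention "at times related to meals and transfers". No width or height of any peak is given. Temporal patterns are the subject of secondary aims (i) and (ii); aim (ii) asks for them by hospital setting and type of ward.

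**The concern.** The F-test estimates error from the scatter of the series about the fitted curve. With one total per hour of the day, that scatter holds two things: the chance variation of the counts, and real structure that a few harmonics cannot follow. A rise lasting a few hours around morning care, or separate rises at meals and transfers, is structure of the second kind. It enlarges the denominator of the test. The chance variation of counts can be estimated from the individual falls, but this test makes no use of that.

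At stake are the secondary aims on temporal patterns. A pattern that is real but not significant gets no reported peak or valley. The risk is largest where counts are smallest, in the hospital and ward-type comparisons. The preventive measures are also said to be adjusted to the patterns found.

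**Working it through.** The article gives no number of falls, power or peak shape, so there is no planned figure to reproduce. The check asks how the stated test behaves under assumed inputs.

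**Inputs.** From the article: least-squares fit, one or more harmonics, F-test of zero amplitude, general level 0.05. Assumed: 24 hourly totals, 1 to 5 harmonics, 150 to 600 falls, and the peak shapes named below.

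**Step 1: what the test requires.** Let PR be the proportion of variance explained by k harmonics. With 24 totals,

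F = (PR / 2k) / ((1 − PR) / (23 − 2k)).

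Solving for PR at the 0.05 critical value, a pattern is significant only if PR exceeds 0.248 (k = 1), 0.379 (k = 2), 0.488 (k = 3) or 0.585 (k = 4). These limits do not depend on the number of falls.

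**Step 2: the limit without chance variation.** With unlimited falls, a single raised block on a flat base has a PR that depends on its width and not on its height.

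| Width of peak | PR, k = 1 / 2 / 3 / 4 | p, k = 1 / 2 / 3 / 4 |
|---|---|---|
| 1 h | 0.087 / 0.174 / 0.261 / 0.348 | 0.38 / 0.43 / 0.46 / 0.47 |
| 2 h | 0.179 / 0.348 / 0.504 / 0.640 | 0.127 / 0.074 / 0.040 / 0.021 |
| 3 h | 0.273 / 0.510 / 0.695 / 0.822 | 0.035 / 0.007 / 0.001 / 0.0002 |

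For the 3-hour peak and k = 1: F = (0.273 / 2) / (0.727 / 21) = 3.94, p = 0.035, only just inside 0.05 even with no chance error. A 1-hour peak is never found at 0.05 with up to four harmonics, however many falls are recorded. A 2-hour peak needs three or more.

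**Step 3: power at 0.05 with 300 falls.** The comparator is a Poisson score test of the same harmonics.

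| Assumed shape | Harmonics | F-test | Count-based test |
|---|---|---|---|
| 07–10 h, 2.5-fold | 1 | 32% | 92% |
| | 3 | 74% | 99% |
| | 4 | 81% | 100% |
| 07–10 h and 18–20 h, 2.2-fold | 2 | 35% | 95% |
| | 5 | 64% | 99% |

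Under a flat rate both tests reject in about 5% of runs, so the gain is not bought with false positives.

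**Step 4: repeat fallers.** With 1.2 falls per patient and a patient-clustered score test, the single 3-hour peak at 300 falls gives 33% (1 harmonic) and 76% (3) for the F-test against 91% and 98%. At 150 falls the figures are 23% and 50% against 59% and 74%. The clustered test kept a size of 4% to 6% at 84 to 300 falls, including when repeat fallers fell at similar hours.

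**Step 5: where the gap closes.** At 300 falls, widening the single peak from 3 to 4 hours raises F-test power from 32% to 66% (1 harmonic) and from 75% to 96% (3). Widening each of the two peaks by an hour raises it from 35% to 74% (2 harmonics) and from 37% to 77% (3). For a smooth cosine with amplitude 40% of the mean, 150 falls and one harmonic, the powers are 83% and 89%. If the series is kept day by hour, the residual is dominated by count variation and the F-test regains the lost power.

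**Step 6: the other threshold.** At p < 0.5 and 300 falls, the single peak is declared in 97.5% to 100% of runs, and the two-peak shape in 97% to 99% with two or more harmonics. Flat data are declared rhythmic in about 50%.

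**The case against.** Several stronger readings are tempting, and the article does not support them.

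- **That the least-squares F-test by itself hides real patterns.** The loss arises only if falls are collapsed to hourly totals. The article does not say so; the hourly wording stands in the Discussion, and building the series is detail that an article may leave to fuller documents. This stands, and makes the point conditional.
- **That the article expects sharp peaks.** It names a morning peak tied to bathing, and meals and transfers as times of risk, but no width. Peaks of a few hours are an inference, and the figures depend heavily on them. The Background also reports that earlier work by the group identified 24-hour patterns.
- **That a single cosine decides.** A multi-component fit is planned without a maximum number of harmonics. It recovers much of the loss: at 600 falls the single peak reaches 97% with four harmonics and the two-peak shape 88% with five. At 150 to 300 falls a clear gap remains.
- **That missed patterns are the main error.** At the p < 0.5 actually written for the Cosinor, the main error is the opposite one, with about half of flat series called rhythmic. That figure conflicts with the general 0.05. Once 0.05 applies, the loss described here applies too.
- **That the programme depends on the F-test.** The Cosinor is described as exploratory, the measures are already listed, none is made conditional on a significant test, and the number of falls is not compared by Cosinor.

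The F-test also holds its nominal size. The issue is power, not validity.

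**Conclusion.** The point holds as a conditional loss of power. With 24 hourly totals tested at 0.05, peaks of a few hours may be missed, most of all by the simple Cosinor and in hospital or ward-type subgroups. The multi-component fit reduces the loss without removing it: in the assumed shapes at 300 falls, the shortfall against a count-based test is about 60 percentage points at worst (32% against 92%, and 35% against 95%) and about 19 at best (81% against 100%). These sizes rest on the assumed bin width, peak width and height, number of harmonics and number of falls, none of which the article gives. It is a worthwhile, inexpensive improvement to a secondary analysis, not an error that invalidates it.

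**What to change.** 1. First reconcile p < 0.5 for the Cosinor with the general p < 0.05.
2. State the unit of the series (hourly totals or day by hour) and the number of harmonics.
3. Keep the Cosinor curve, MESOR, amplitude, peak and valley for description.
4. Base significance on Poisson harmonic regression, or its score test, with the same harmonics. Cluster the variance by patient, since one patient may fall several times. For the anonymised Phase 2 records, cluster by hospital-day.
5. Report the lack of fit of the hourly totals to the curve separately, so that a significant pattern with a poorly fitting curve is seen as such.

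In the peaked and cosine shapes examined, the count-based test matched or beat the F-test. No new data are needed. The cost is analysis wording, a standard statistics package beside Chronolab, and slightly more analysis work.

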## Methods/design

### Aims

The main aim of this study will measure the effect of the implementation of a falls prevention programme based on temporal patterns and relative risks factors.

Secondary aims will be: (i) to identify temporal patterns in the incidence of hospital falls and intrinsic and external risks factors, pre- and post-intervention; (ii) to establish differences in temporal patterns according to the hospital setting (teaching or non-teaching) and the different types of wards (medical, surgical or mixed), pre- and post-intervention; (iii) to study the role of circadian time in drug administration for older people suffering from hospital falls, pre- and post-intervention; (iv) to identify the level of fatigue/sleepiness, attention and cognitive functionality of healthcare professionals intervening during hospital falls, pre- and post-intervention; and (v) to develop a uniform, simple and intuitive method to record hospital falls in order to improve the effectiveness of the registration of falls and to assess the implementation pre- and post-intervention.

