### Data analysis

***Phases 1 and 2.*** For the analysis of quantitative data, descriptive statistics will be used, including measures of frequency, central tendency and dispersion according to the type of variable (quantitative or qualitative). Normality will be calculated with Shapiro-Wilk’s test and homogeneity with Levene’s test. To compare proportions of categorical variables, the chi-square test for contingency tables will be used. In the case of 2 × 2 tables, such tests with Yates correction will be used, and if the expected frequency is ≤ 5, Fisher’s exact test will be used. To compare mean values between the quantitative variables of two groups, Student’s t test for independent samples will be used. For the comparison of the mean values between quantitative variables and hospitals, the one-factor ANOVA test and ad-hoc tests with correction by GT2 Hochberg (if variance is homogeneous) or Games Howell (if variance is unequal) will be used. For the correlation between the quantitative variables, Pearson’s correlation coefficient will be used. For the logistic regression, multivariate analysis will be used.

All hypothesis tests will be bilateral. All tests with a confidence level of 95 % (p < 0.05) will be considered statistically significant.

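### The Cosinor test that the protocol states cannot establish the differences in temporal pattern that aim (ii) seeks; a direct between-group test is needed

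*Protocol article*

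**What the plan says.** The second of the secondary aims (Aims section) is "to establish differences in temporal patterns according to the hospital setting (teaching or non-teaching) and the different types of wards", pre- and post-intervention. This is a comparison between groups.

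The Data analysis section describes the Cosinor method in some detail: least-squares fitting, one or more harmonics, proportion of variance explained, an F-test, bands for the relative amplitude, and the software. The F-test "was used to reject the null hypothesis of zero amplitude". A pattern counts as verified once that test is significant, and the summary measures follow from there: "The descriptive parameters of the statistically significant temporal patterns are the statistical estimated mean rhythm line", with amplitude, peak and valley after it. No test or interval for a difference in amplitude, peak time or curve between two series appears.

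The same section first lists general tests (chi-square, t test, one-way ANOVA across hospitals, correlation, logistic regression). None is tied to aim (ii).

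**The concern.** The null hypothesis of the stated test concerns one series at a time. Two wards can both reject zero amplitude and have opposite peaks. Two wards can also share the same rhythm while only the larger one rejects, because rejection depends heavily on the number of falls in the series. So neither agreement nor disagreement of the verdicts answers aim (ii).

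The significance gate makes this worse. A series that is not significant has no verified pattern, and no parameters are promised for it, so the reader is left with a rhythm in one stratum and none in another. Where both are significant, the reader has two sets of point estimates with no stated measure of the uncertainty of their difference.

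The strata are likely to be unequal: one university hospital against three regional ones, three ward types, and 18 months against 15. A rhythm that seems to fade in a smaller stratum or after the intervention could be taken for an effect of time-adjusted prevention when it reflects only fewer falls.

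**Working it through.** The article gives no sample size, expected number of falls or amplitude for aim (ii), so there is no figure to reproduce. The check asks what would happen if separate verdicts were used to compare groups.

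**Inputs from the article (Data analysis).** Zero-amplitude F-test per series; general threshold "p < 0.05) will be considered statistically significant"; amplitude defined as the difference between peak and valley; relative amplitude called moderate at 26–50 and high above 50.

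**Assumed inputs.** 60 to 600 falls per series; semi-amplitude (half of peak to valley) mainly 25% or 50% of MESOR. By the article's definition these are relative amplitudes of 50 (top of its moderate band) and 100 (high).

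**Step 1, formula.** If q1 and q2 are the probabilities that each series is significant, two independent series with the same true rhythm disagree with probability q1(1 − q2) + q2(1 − q1). With equal power q this is 2q(1 − q): 50% at q = 0.5, 32% at q = 0.8, 9.5% at q = 0.95. For three ward types it is 1 − q³ − (1 − q)³: 75%, 48% and 14%.

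**Step 2, simulation.** 40,000 pairs of series, each of 24 hourly Poisson counts, identical true 24 h curve, least-squares Cosinor, F on 2 and 21 df, threshold 0.05. At semi-amplitude 25%:
- 300 v 100 falls: power 0.724 and 0.292. 0.724 × 0.708 + 0.292 × 0.276 = 0.513 + 0.081 = 0.593.
- 300 v 150: power 0.726 and 0.417. 0.726 × 0.583 + 0.417 × 0.274 = 0.423 + 0.114 = 0.538 (simulated 0.537; repeat runs 53 to 54%).
- 400 v 250: power 0.848 and 0.641. 0.848 × 0.359 + 0.641 × 0.152 = 0.304 + 0.097 = 0.402 (simulated 0.40).

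At semi-amplitude 50% the same three settings give 14 to 15%, 4% and 0.2%.

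**Step 3, comparing point estimates by eye.** At semi-amplitude 25% the estimated peak time has an SD of about 2.7 h with 100 falls and 1.3 to 1.4 h with 300. With 300 v 100 falls and identical curves, the two peaks lie more than 2 h apart in about 35% of the pairs in which both series are significant.

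**Step 4, the opposite error.** With a true 6-hour difference in peak, semi-amplitude 50% and 200 falls in each series, both series are significant in 98% of runs and the verdicts disagree in only 1.7%. The verdicts carry almost no information about a large real shift.

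**Step 5, a direct test.** A joint group-by-harmonic F-test at 0.05 calls identical patterns different in 4.0% to 5.3% of runs over all scenarios and detects the 6-hour shift in 99%. A Poisson likelihood-ratio version rejected in 6.6% of 1,500 runs with identical curves at 300 v 100 falls, so slightly above nominal.

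**Sensitivity to the printed threshold.** The Cosinor text prints a different cut-off: "The statistical significance of temporal patterns will be verified when the null hypothesis rejected for the F-test statistic is p < 0.5". At 0.5 and semi-amplitude 25% the three settings give 18%, 11% and 4%; with no rhythm at all, two series disagree in 50% of runs. That inconsistency is a separate matter, and the present point holds at either threshold.

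**The case against.** The strongest objection is that the harmful decision rule is not in the text. The article presents Cosinor as exploratory, calls its parameters descriptive, and never says that groups will be declared different because one series is significant and another is not. The zero-amplitude test is valid for the question it is given. This stands, and it rules out the stronger reading a reader might infer, that identical patterns will often be declared different. That would need a rule the article does not contain, and event counts and amplitudes it does not give.

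Second, an article condenses a fuller plan, which may name a comparison of rhythms. That is possible, and a missing detail alone would be no finding. But the article does fix the Cosinor inference, in detail, and what it fixes answers a different question from aim (ii).

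Third, the general tests could bear on timing: time of fall is recorded by hour and minute, day and shift (Study variables), so shift could be cross-tabulated with ward type by chi-square. True, but the article does not link this to aim (ii), and a chi-square on shift tests neither amplitude nor peak time. A t test or ANOVA on clock time would ignore that time is circular.

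Fourth, two extensions fail. Aim (i) speaks of identifying patterns, which a Cosinor per series can do, so the point rests on aim (ii) alone. Nor can one say that the post period will appear to lose its rhythm: 18 against 15 months is a ratio of 1.2. With 300 v 250 falls at semi-amplitude 25%, apparent loss occurs in 26% of runs and apparent gain in 18%; at semi-amplitude 50% total discordance is 0.2%.

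**Conclusion.** The point holds in limited form: as stated, the Cosinor analysis cannot establish the between-group differences that aim (ii) asks for. This follows from the null hypothesis itself and needs no assumption.

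The size of the possible error does need assumptions. If separate verdicts were used, false differences would range from near zero (strong rhythm, large and balanced series) to more than half of comparisons (moderate rhythm, unequal series), and a large real shift could pass unnoticed. These figures assume hourly Poisson counts, a sinusoidal 24 h rhythm and the fall counts shown. They describe what the plan leaves open, not what its authors have said they will do. Because the aim is secondary, this should be corrected but does not touch the main outcome.

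**What to change.** For each aim (ii) comparison (setting, ward type, pre against post), fit one harmonic model to all groups with the same harmonics, and test group x cosine and group x sine jointly: 2 df per harmonic for two groups, 4 df per harmonic for three ward types. Fit it on a relative scale (for example Poisson regression with a log link and a group main effect), so that a mere difference in the number of falls is not read as a difference in pattern. Report the difference in relative amplitude and in peak time with 95% CIs, for all groups whether or not their own zero-amplitude test is significant. Add a sentence that separate zero-amplitude results are not evidence of a difference between groups.

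The cost is a few lines of text and a little extra analysis of hourly counts already collected. The joint model may have to be run outside the named Cosinor software, in any standard statistical package.

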In the case of healthcare professionals, independent variables will be: (i) sociodemographic and economic data (age, gender, marital status, level of education, work experience and time worked in the unit); (ii) kind of contract and work unit; (iii) sleep pattern (quality and quantity of hours); (iv) chronotype measured by the Horne-Östberg Questionnaire (1976); (v) quality of life in terms of body functionality, physical limitations, body pain, social role or function, mental health, emotional limitations, vitality, energy or fatigue and general perception about own health; (vi) general health status in terms of somatic symptoms, anxiety, insomnia, social dysfunction and depression; and (vii) fatigue/sleepiness, attention and cognitive functionality.

Pre- and post-intervention will be:

***Step 1.*** Before implementing preventive measures: development of audits and seminars in order to improve, secure and control the registration of falls in hospitals and related factors, as well as others study variables (quality of life, functional status, chronotype, fatigue/sleepiness, attention and cognitive functionality). These interventions will be carried out by research nurses who are working in hospitals.

***Step 2.*** Implementation of a preventive measures programme: adjusted to the identification of temporal patterns of falls and relative risk factors of falls. As measures will be agreed with the managers of hospital centres, the interventions will be reflected in the official document of general objectives of the hospitals. Official document to which the personnel involved in the intervention have access. Preventive measures will be focused on organizational, educational and behavioural elements related to older people and healthcare professionals:

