After obtaining and analysing the falls that occurred during the first 18 months of the study, time-adjusted preventive measures will be carried out. These measures will be focused on organizational, educational and behavioural elements (previously mentioned).

The establishment of the programme of time-adjusted prevention measures will be carried out in May 2019 in the four centres. The post-intervention data collection will cover July 2019 to September 2020. The managers responsible for each centre, together with the research team, will implement the measures, and, as in the first phase, seminars will be held with healthcare professionals to focus on the recording of falls and their circumstances, as well as the variables included in the prevention programme.

During the post-intervention phase, the individual monthly audits will continue to be carried out with each Clinical Management Unit. This follow-up will make it possible to discern the effectiveness of the preventive measures.

***Phase 2***: For the retrospective study, the data will be delivered by the centres participating in the project to the Principal Investigator anonymized.

***Phase 3***: The development of the focus groups will be carried out in the facilities of the participating hospitals, ensuring the confidentiality of the participants. Four focus groups will be held at the Reina Sofia University Hospital in Córdoba and one in each of the three regional centres.

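### The Cosinor significance threshold is printed as p < 0.5, against p < 0.05 for all tests; applied as written, about half of rhythm-free series would be called significant

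*Protocol article*

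**What the plan says.** All the statistical wording comes from the Data analysis section of the protocol article.

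- **General rule for Phases 1 and 2.** "All hypothesis tests will be bilateral", followed by "All tests with a confidence level of 95 % (p < 0.05) will be considered statistically significant".
- **Cosinor test.** An F-test comparing the fitted cosine with a linear approximation "was used to reject the null hypothesis of zero amplitude (absence of cyclical variation with respect to the period of time explored").
- **Cosinor threshold.** "The statistical significance of temporal patterns will be verified when the null hypothesis rejected for the F-test statistic is p < 0.5".
- **What follows from passing.** "The descriptive parameters of the statistically significant temporal patterns are the statistical estimated mean rhythm line", together with amplitude, peak and valley. The p-value therefore decides which patterns are described.

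Two other sections link the patterns to the intervention. Under Study variables, the step 2 programme is "adjusted to the identification of temporal patterns of falls and relative risk factors of falls". Under Data collection: Procedure, the order is given: "After obtaining and analysing the falls that occurred during the first 18 months of the study, time-adjusted preventive measures will be carried out".

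**The concern.** The zero-amplitude F-test is a hypothesis test, so the general rule covers it, and the Cosinor paragraph then gives it a threshold ten times larger. The two cannot both hold. A reader who lets the specific provision override the general one would use 0.5, which gives almost no protection against calling noise a rhythm.

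Three things are at stake:

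- **Secondary aims (i) and (ii).** These concern temporal patterns of falls and how they differ by hospital setting and ward type. Patterns reported under them could include many that arose by chance.
- **The prevention programme.** It is said to be adjusted to the patterns found in the first 18 months, so a chance pattern could inform it.
- **Prespecification.** A rhythm with p = 0.2 could be reported as significant by the published rule, and readers could not tell which threshold had been fixed in advance.

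**Working it through.** **Inputs from the article.** Confidence level 95 %; general threshold 0.05; Cosinor threshold 0.5; two-sided tests; null hypothesis of zero amplitude. The article gives no number of time bins or falls per bin, so the settings used below are assumptions.

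**Step 1. Which threshold matches the stated confidence level?** Alpha = 1 − 0.95 = 0.05. This reproduces the general rule and not the Cosinor rule. Sidedness cannot explain the gap. The F-test is an omnibus test of zero amplitude, and no one- or two-sided variant of a 95 % level gives 0.5.

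**Step 2. False-positive rate per rhythm-free series.** When the null hypothesis is true, a valid test rejects with probability alpha: 50 % at 0.5 and 5 % at 0.05, a ratio of 0.5 / 0.05 = 10. A least-squares Cosinor F-test was run on 20,000 simulated series without rhythm in each setting:

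| Time bins | Harmonics fitted | Data (mean per bin) | Rejected at 0.5 | Rejected at 0.05 |
|---|---|---|---|---|
| 24 | 1 | normal | 0.4966 | 0.0483 |
| 24 | 1 | Poisson (10) | 0.5002 | 0.0525 |
| 24 | 1 | Poisson (2) | 0.5056 | 0.0503 |
| 24 | 2 | Poisson (10) | 0.4955 | 0.0475 |
| 24 | 3 | Poisson (10) | 0.5037 | 0.0503 |
| 12 | 1 | Poisson (20) | 0.5017 | 0.0502 |
| 7 | 1 | Poisson (30) | 0.5054 | 0.0515 |

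The range is 49.6 % to 50.6 % at 0.5 and 4.8 % to 5.3 % at 0.05. The assumed settings hardly matter.

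**Step 3. How weak a fit would pass?** The article measures fit by the proportion of variance explained (PR). For one harmonic and n bins the F-test has 2 and n − 3 degrees of freedom, and p = (1 − PR)^((n − 3)/2). With n = 24 the exponent is 21/2, so the PR at the threshold is 1 − p^(2/21):

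- p = 0.5: PR = 1 − 0.5^(2/21) = 0.0639
- p = 0.05: PR = 1 − 0.05^(2/21) = 0.2482

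With 24 hourly bins, a cosine explaining about 6.4 % of the variance would pass at 0.5. At 0.05 it must explain about 24.8 %.

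**The case against.** The strongest reply is that this is a misprint. The blanket rule of p < 0.05 stands just before the Cosinor paragraph, nothing defends 0.5, and an analyst would very likely use 0.05. That is probably true, and the harm then arises only if the text is followed literally. The contradiction still stands in a published decision rule, and the wrong value is in the sentence that governs this test.

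The bands for percentage amplitude do not answer the point either. They grade how prominent a pattern is and do not replace the significance rule.

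A reader might infer more than the article supports:

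- **That the main result is affected.** The main aim is the effect of the programme and the main dependent variable is the number of falls. Cosinor is used to explore temporal patterns, which are secondary aims, and the 0.5 rule does not apply to the main comparison.
- **That pre/post differences in pattern would rest on chance.** The rule tests zero amplitude within one series. It does not test a difference between periods.
- **That the programme would be built on noise.** Its measures are already listed under Study variables, most carry no clock time, and the one timed item, on meals and transfers, is already named. Nothing says that a p-value alone switches a measure on. The stated adjustment to identified patterns remains, so chance patterns could inform the programme, but no more can be said.
- **That a total of false rhythms, or a much higher rate from trying several harmonics, can be given.** The article states neither the number of series nor a rule that any one of several separately tested components suffices. The false-positive rate applies only to series with no rhythm, and the Background reports real 24-hour and seasonal patterns in earlier work.

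**Conclusion.** The point holds as a contradiction between two thresholds for the same test, with the Cosinor value wrong and probably a misprint. Applied as written, the rule would declare about 50 % of rhythm-free series significant instead of about 5 %. That size follows from the threshold itself and assumes only that the F-test keeps its nominal level, which the simulations bear out. The 6.4 % and 24.8 % figures for variance explained further assume 24 hourly bins and one harmonic.

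The reach is limited to secondary aims (i) and (ii) and to the patterns that may inform the programme. Because the threshold decides which patterns are reported as significant, this is more than a clerical matter, even though the correction is very small.

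**What to change.** In the Cosinor paragraph of Data analysis, change p < 0.5 to p < 0.05, so that it agrees with the general rule in the same section.

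Also confirm which threshold was used in any Cosinor analysis already done. The article places the start of the programme in May 2019, after analysis of the first-step falls, so such an analysis may already exist. If 0.5 was applied, the patterns need to be judged again at 0.05.

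The text change is one line. Its cost is that some weak rhythms will no longer be called significant. The contradiction does not call for a further correction for the number of harmonics; such detail is commonly left to a full analysis plan, which is not shown.
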